### Statistical methods

#### Primary analysis

Change from baseline in percentage of adherent days at month 6 will be linearly regressed on the (i) study arm (VP vs. UC), (ii) baseline percentage of adherent days, (iii) change in number of daily doses taken in order to correct for potential medication change or number of eCAPs™ tracked, and (iv) other baseline characteristics (age, language spoken, income, IOP, BIPQ and BMQ scores) in order to increase statistical efficiency. The linear model will be estimated via ordinary least squares (OLS) and the hypothesis of equality between the mean change in primary outcome between the study arms will be tested by testing whether the binary variable indicating the study arms equals zero using a *t* test. All tests will be bilateral, performed at the 5 % level of statistical significance, and carried out using the statistical software Stata version 13.1 (StataCorp LP, College Station, TX, USA).

The analysis will be performed according to an intention-to-treat approach. If multiple medication users have faulty devices, adherence will be calculated based on functioning devices. Remaining missing adherence data will be imputed using Markov chain Monte Carlo multiple imputation including as predictors all factors mentioned above. In addition, for sensitivity analysis, baseline adherence will be carried forward for patients who withdraw from the study as those VP patients who do not achieve their goals might disproportionally withdraw from the study.

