### Outcome measures

#### Primary outcome

Our primary outcome is the *mean change from baseline in percentage of adherent days at month 6*. A day will be counted as adherent when the patients take all their medication(s) within the appropriate dosing windows for the day. The percentage of adherent days during month 1 (baseline) and month 6 will be calculated for each patient and the difference in mean change between study arms will be tested. The primary outcome is directly incentivized in the VP arm and not incentivized in the UC arm. As a result, this outcome will appropriately capture the behavioural change induced by value pricing, if any.

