### Randomization

A computerized random number generator (sealed envelope™) was used by the study principal investigator (PI) and coordinator at Duke-NUS to create an assignment schedule to allocate eligible participants into one of the two study arms in ratio of 1:1. Randomization was stratified according to the number of glaucoma medications prescribed to patients (one versus multiple eye drops) given that medication adherence has been shown to be highly correlated with this factor [44]. For allocation concealment, the study PI and project coordinator enclosed the assignments in sequentially numbered, opaque, sealed randomization envelopes before handing them to the research optometrist on site. Blocking size will not be disclosed to the study site to protect concealment. Note that the behavioural nature of the intervention precludes masking the arm allocation to both the study team and patient. Arm allocation will be revealed at the end of the 1-month baseline measurement of medication adherence (see Fig. 2).

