#### Secondary analyses

The same analysis described above will be conducted for the change from baseline in percentage of adherent days from months 2 to 6 in order to analyse the trajectory of adherence change induced by the intervention. All months will be simultaneously analysed and standard errors will be adjusted for individual clustering. Next, logistic regressions of indicator variables indicating whether the 75 % and 90 % adherence goals are achieved will be estimated from months 2 to 6. Regressors will include the study arm, a variable indicating whether the adherence goal was achieved at baseline, change in number of daily doses taken and the same baseline characteristics as for the primary analysis.

Changes from baseline in IOP and GQL-15 and EQ5D-5 L scores at month 6 will be linearly regressed on the study arm, their baseline values, and the same other baseline characteristics as for the primary analysis. If the intervention shows improvements (relative to the control group) both in terms of GQL-15 and EQ5D-5 L scores, we will conduct an economic analysis using utilities derived from the change in EQ5D-5 L score. The costs will be obtained from the financial incentives paid during the last month of the trial and from assumptions on operational and administrative costs incurred if the intervention were to be scaled up. The perspective of the analysis will be that of a governmental agency subsidizing healthcare costs.

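### The primary and other adherence models adjust for change in daily doses, a post-allocation variable, so the arm coefficient is the intention-to-treat effect only if arm does not affect dose change

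*Protocol article*

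**What the plan says.** Under Primary analysis, change in percentage of adherent days at month 6 is regressed by ordinary least squares on study arm, baseline adherence, "change in number of daily doses taken in order to correct for potential medication change" (or for the number of devices tracked), and "other baseline characteristics (age, language spoken, income, IOP, BIPQ and BMQ scores) in order to increase statistical efficiency". The primary hypothesis is tested by "testing whether the binary variable indicating the study arms equals zero". The same section states: "The analysis will be performed according to an intention-to-treat approach".

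The timing comes from two other sections. Under Primary outcome, "The percentage of adherent days during month 1 (baseline) and month 6 will be calculated for each patient". Under Randomization, "Arm allocation will be revealed at the end of the 1-month baseline measurement of medication adherence".

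Under Secondary analyses, the goal-attainment logistic models list "change in number of daily doses taken and the same baseline characteristics as for the primary analysis". The months 2 to 6 analysis, and the alternative adherence measures under Explanatory analyses, take the covariate over because they repeat the primary analysis. The one sensitivity analysis described carries baseline adherence forward for patients who withdraw. No adherence model without the dose-change covariate is described.

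**The concern.** The primary objective asks whether adding rebates to usual care is superior to usual care alone. That is a total effect of being offered rebates. Conditioning on something that happens after allocation can turn the arm coefficient into an effect with that variable held fixed, which answers a different question and is not protected by randomisation.

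There are plausible routes from arm to dose change. The first secondary objective expects value pricing to improve intraocular pressure, which is what the eye drops are there to control, so better adherence could alter later prescribing. Devices can also be lost or fail after allocation, which changes the number tracked. At stake is the estimate behind the trial's one confirmatory test.

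**Working it through.** **1. The plan's own figure.** Inputs from Sample size: difference 10 points, SD 16.3, two-sided 5%, power 80%. Per arm n = 2 × (1.960 + 0.842)² × 16.3² / 10² = 2 × 7.849 × 265.69 / 100 = 41.7, so 42, or 84 in total. Multiplying by 1.2 for attrition gives 100.8, in line with the stated 100. (Dividing by 0.8 would give 105; that is a separate matter.) This is an unadjusted comparison of two means. The disputed covariate does not enter it, and removing the covariate changes no stated figure.

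**2. Is the covariate post-allocation?** Baseline is month 1 and arm is revealed at its end. A change from baseline to month 6 is therefore realised after patients know their arm. Every other covariate is a baseline measurement.

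**3. Scheduled or tracked doses: size of the gap.** The gap between the total effect and the adjusted coefficient is

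points lost per added daily dose × difference in escalation rates × doses added.

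All inputs are assumptions: escalation in 15-20% of usual-care and 5-10% of value-pricing patients, and 5-15 points lost per added dose.

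- Smallest: 5 × (0.15 − 0.10) × 1 = 0.25, about 0.3 points.
- Largest: 15 × (0.20 − 0.05) × 1 = 2.25, about 2.3 points.
- Largest with two added doses: 15 × 0.15 × 2 = 4.5 points, which needs every input at its extreme.

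**4. When the gap vanishes and when it grows.** Regressions were run on simulated data (400,000 patients per scenario) with assumed inputs: effect with dose change held fixed 10 points, residual SD 16.3, SD of dose change 0.5, and 10 points lost per extra dose.

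| Arm shifts mean dose change by | Total effect | Adjusted coefficient | Adjusted, if dose change also correlates −0.3 with unmeasured causes of adherence |
|---|---|---|---|
| 0 | about 10 | about 10 | about 10 |
| −0.2 dose | about 12 | about 10 | about 8 |
| +0.2 dose | about 8 | about 10 | about 12 |

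With no shift there is no bias. With a shift, the adjusted coefficient departs from the total effect in either direction. Shared unmeasured causes widen the difference.

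**5. Literal reading: doses actually taken.** Suppose two doses a day, a true effect of 10, and covariate = 2 × outcome / 100 + noise of SD s. The adjusted coefficient is 10 × s² / (s² + (0.02 × 16.3)²), with (0.02 × 16.3)² = 0.1063.

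- s = 1.0: 10 × 1 / 1.1063 = 9.0
- s = 0.5: 10 × 0.25 / 0.3563 = 7.0
- s = 0.3: 10 × 0.09 / 0.1963 = 4.6
- s = 0.1: 10 × 0.01 / 0.1163 = 0.9

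Simulation gave 9.1, 7.0, 4.6 and 0.8. The answer depends almost entirely on the assumed noise.

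**The case against.** Much can be said for the plan, and most of it limits the point without removing it.

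- **The literal reading is not the likely one.** A reader might infer that the adjustment wipes out the treatment effect. The stated purpose, correcting for medication change or the number of devices tracked, fits scheduled or tracked doses and not doses missed through non-adherence. The protocol also separates doses taken in the window from doses taken at any time, so even literally the covariate is not simply the outcome again. The near-zero results in step 5 should not be used to size the problem. They show only why the wording has to be tightened.
- **Bias is conditional.** A reader might infer that the primary estimate is certainly biased. It is not biased if arm leaves dose change untouched.
- **The pressure route does not by itself create false positives.** If rebates do not change adherence, that route is closed and the test keeps its size. If they do, less escalation under value pricing makes the adjusted effect smaller, which is conservative for superiority. This stands for that route. It does not cover device loss or handling that differs by arm.
- **The schedule limits regimen changes.** Check-ups run from every 3 months to yearly, the month 3 collection is by courier, and a change made at the month 6 visit comes too late to matter. Lost or broken devices are replaced. The protocol says that study team and patient are unmasked but does not say whether the treating ophthalmologist learns the arm. All this argues for a modest gap, but the plan itself expects medication changes.
- **The intervention is said not to affect standard of care.** That statement justifies having no monitoring committee. It does not exclude regimen changes that follow from better adherence.
- **The covariate serves a real purpose.** Adherence is calculated on functioning devices only, so fewer tracked devices make an adherent day easier to reach. This stands: deleting the covariate alone would leave that artefact in place.

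**Conclusion.** The point holds in a conditional form. The adherence models include a variable realised after allocation while the plan declares intention-to-treat, and no model without it is described. The arm coefficient is the intention-to-treat effect only if arm does not affect dose change, and nothing in an open-label design secures that. On the likelier reading the gap is about 0.3 to 2.3 points against a 10-point target. That range rests wholly on assumed escalation rates and assumed points lost per dose, because the protocol supplies neither.

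The scope is the primary model, the months 2 to 6 model, the 75% and 90% goal models, and the alternative adherence measures. A reader might infer that every secondary model is affected. The documents do not support this: the intraocular pressure, GQL-15 and EQ-5D-5L models list arm, baseline values and the other baseline characteristics, without dose change.

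**What to change.** 1. For the primary and all other adherence comparisons between arms, use study arm, baseline adherence (or baseline goal attainment), the number of prescribed daily doses at baseline or the single/multiple-medication stratum, and the listed baseline characteristics.
2. Handle changes in tracked devices in the outcome. Either compute month 1 and month 6 adherence on a consistent set of tracked devices, or treat data from failed devices as missing and impute them, so that fewer tracked devices cannot inflate adherence.
3. Reword the covariate as change in scheduled or tracked daily doses, and keep the model that adjusts for it as a labelled sensitivity analysis.

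The cost is a few sentences. The baseline checklist already records the medication regimen, and sample size, significance level and power stay as stated. The downside is some residual noise from regimen changes. The change should be dated and recorded before the final analysis, since outcomes by arm are to be computed after 25, 50 and 75 completers.

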## Methods

### Trial design

The Study on Incentives for Glaucoma Medications Adherence (SIGMA) trial is designed as a randomized, controlled, open-label, single-centre superiority trial with two parallel arms. A total of 100 non-adherent glaucoma patients will be block-randomized (blocking factor: single versus multiple medication users) into the UC and VP arms in a 1:1 ratio. Baseline assessment lasts 1 month, followed by a 5-month intervention. The primary outcome is medication adherence as recorded by an electronic medication container.

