#### Explanatory analyses

The same analysis as for the primary outcome will be performed using the alternative measures of medication adherence listed in the explanatory outcomes section. Next, the models used in the primary and secondary analyses will be extended by adding interaction terms between potential intervention moderators (presence of comorbidities, glaucoma- and non-glaucoma-related medication regimen, potential incentive amount, BIPQ and BMQ variables, and patient sociodemographic characteristics) and the binary variable indicating study arms. Last, medication adherence levels at baseline will be linearly regressed on potential factors of medication adherence (presence of comorbidities, glaucoma- and non-glaucoma-related medication regimen, BIPQ and BMQ variables, and patient sociodemographic characteristics).

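### The primary model leaves out the randomisation stratum (one versus multiple drops); if the stratum predicts adherence change beyond baseline adherence, the reported standard error is slightly too large and the test conservative

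*Protocol article*

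**What the plan says.** The Trial design section of the protocol article says that patients will be "block-randomized (blocking factor: single versus multiple medication users) into the UC and VP arms in a 1:1 ratio". The Randomization section gives the reason: "medication adherence has been shown to be highly correlated with this factor".

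The Primary analysis section specifies the model term by term. Change in adherent days at month 6 is "linearly regressed on the (i) study arm (VP vs. UC), (ii) baseline percentage of adherent days". Item (iii) is "change in number of daily doses taken in order to correct for potential medication change" or in the number of devices tracked. Item (iv) is "other baseline characteristics (age, language spoken, income, IOP, BIPQ and BMQ scores) in order to increase statistical efficiency". The parenthesis in item (iv) enumerates its contents and does not offer them as examples. Neither the stratum nor any other baseline count of drops is among them.

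Missing adherence data are handled by "Markov chain Monte Carlo multiple imputation including as predictors all factors mentioned above", so the stratum is absent from the imputation as well. The Secondary analyses section applies the same model to months 2 to 6 and carries the same baseline characteristics into the logistic models for the 75% and 90% goals and into the IOP and quality-of-life models. Treatment regimen enters only in the Explanatory analyses, among the possible moderators ("glaucoma- and non-glaucoma-related medication regimen, potential incentive amount") and among the correlates of baseline adherence.

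**The concern.** A factor is normally used for stratification because it is prognostic. Balancing it removes most of its contribution from the true sampling variance of the arm comparison. The analysis reflects that reduction only if the factor is in the model. Otherwise the between-stratum variance stays in the residual mean square and the reported standard error overstates the actual uncertainty.

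Here the covariates in item (iv) are justified by statistical efficiency, yet the one factor that the protocol itself calls highly correlated with adherence is not among them. Item (iii) is no substitute. It measures change during follow-up, so a patient stable on one drop and a patient stable on three both score zero. There is also a reason to expect some residual association: a day counts as non-adherent if a single dose is missed, so more drops give more ways to fail.

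At stake is a somewhat wide interval and a somewhat conservative test, in an analysis that does not follow the groups within which patients were randomised.

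**Working it through.** **Inputs from the Sample size section:** difference 10 percentage points, SD at most 16.3, two-sided 5%, power 80%, attrition at most 20%, total 100.

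**Assumed, because the protocol gives no value:** R², the partial R-squared of the stratum given the other covariates, taken from 0 to 10%. The value 16.3 is used as the residual SD of the model without the stratum, for illustration only.

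**1. The plan's own figure.** n per arm = 2 × [16.3 × (1.960 + 0.842) / 10]² = 41.7, so 42 per arm and 84 evaluable patients. 84 × 1.2 = 100.8, which agrees with the stated 100. With 20% attrition, 100 patients leave 80 completers, 40 per arm. Power is then 78.3% by the normal approximation and 77.3% by the noncentral t, which is used below.

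**2. Overstatement of the standard error.** Reported SE without the stratum / SE with it = 1/√(1 − R²).

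**3. Actual type I error when the stratum is omitted.** Approximately 2 × [1 − Φ(1.960/√(1 − R²))].

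**4. Power with the stratum included.** Residual SD = 16.3 × √(1 − R²). Noncentrality = 10 / (residual SD × √(2/40)). At R² = 0 this is 10/3.645 = 2.74. At R² = 10% the residual SD is 15.46 and the noncentrality is 10/3.458 = 2.89.

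| Assumed R² | SE ratio | Type I error if omitted | Power if included |
|---|---|---|---|
| 0% | 1.000 | 5.0% | 77.3% |
| 2% | 1.010 | 4.8% | 78.1% |
| 5% | 1.026 | 4.4% | 79.4% |
| 10% | 1.054 | 3.9% | 81.5% |

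**5. Check by simulation.** Settings, all assumed: 80 completers, equal strata, blocks of 4 within stratum, stratum–baseline correlation 0.4, six further covariates unrelated to outcome, 6,000 runs per setting. The Monte Carlo error of a 5% rejection rate is √(0.05 × 0.95/6000), or about 0.3 points.

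- R² = 0: the two models agree (type I error 4.9% without the stratum and 5.0% with it; power 73.5% and 73.3%).
- R² = 5%: adding the stratum lowers the mean reported SE from 3.81 to 3.72, while the empirical SE hardly moves (3.81 to 3.79). Type I error is 5.1% without and 5.6% with the stratum, so an effect of this size is barely visible above simulation noise. Power is 73.3% and 74.8%.
- R² = 10%: without the stratum, the reported SE is 3.81 against an empirical 3.67, type I error 3.9%, power 73.8%. With it, the reported SE is 3.61 against an empirical 3.62, type I error 4.8%, power 77.3%.

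So at R² = 10% the reported SE is overstated by about 5% (3.81/3.61), whereas the true SE falls by only about 1.4% (3.67 to 3.62). Simulated power is lower throughout than in the table because the simulated model also carries the other covariates. The simulated gain at R² = 10% is 3.5 points (73.8% to 77.3%), against 4.2 points (77.3% to 81.5%) in the table. The table figure is therefore better read as an upper value.

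**The case against.** The strongest objection concerns size. The correlation cited in the Randomization section is with adherence, whereas what matters here is the stratum's association with month-6 change after adjustment for baseline adherent days. Baseline is scored by the same all-or-none daily rule, so the penalty for having several drops is already in the baseline value, and much of the association may be absorbed there. The true R² could be zero, in which case nothing is lost. This stands, and it is why the range starts at 0. One month of baseline measures the tendency with noise, so some residual association is plausible, but the documents do not show it.

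A reader might infer that the trial gives up substantial precision. It does not, because stratified randomisation has already secured most of the gain in the true variance. The loss lies mainly in the reported standard error.

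A reader might also infer from 77.3% that the planned analysis is underpowered. The documents do not support that. They give 16.3 as a maximum SD for monthly adherence, not as the residual SD of a model adjusted for baseline adherence and several other covariates. The figure shows the scale of the effect and is not the power of the planned analysis.

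It can also be said that regimen is not ignored, since it appears as a moderator in the Explanatory analyses. That is true, but it does not alter the primary test.

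Finally, a separate analysis plan may exist. The point does not rest on a missing detail, however: the article fixes the primary covariates one by one.

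**Conclusion.** The concern holds as a modest efficiency point. That the stratum is missing from the enumerated primary covariates, and from the imputation and secondary adherence models that reuse them, is plain from the text. The direction is also clear: if the stratum is prognostic beyond baseline adherence, the reported standard error is too large, the interval too wide and the test conservative.

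The size is not known. It is 0 to 5% of the reported standard error for an assumed partial R-squared of 0 to 10%, and at most about 4 points of power at the illustrative SD of 16.3 with 40 per arm.

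It would be wrong to conclude that the omission biases the treatment effect or raises the false-positive rate. The factor is balanced by design, and the error in the test runs the other way. For the logistic goal models the SE ratio above does not apply, and no size is claimed there. For IOP and quality of life, the documents do not tie the factor to the outcome.

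**What to change.** Add a binary indicator of one versus multiple glaucoma drops, as recorded at randomisation, as a fixed covariate in:

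- the primary model;
- the secondary adherence models (months 2 to 6, and the 75% and 90% goals);
- the multiple-imputation model.

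Its inclusion in the IOP and quality-of-life models is optional and would serve only consistency with the design. Item (iii) can stay as it is, since it serves a different purpose.

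The cost is one line in the analysis plan and one degree of freedom per model. No new data are needed, because the stratum is known for every randomised patient.

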### Study arms

In this study, patients learn about their arm allocation by phone 1 month after their enrolment. This is to collect 1 month of baseline data on medication adherence. The patients then remain in their respective study arm for a duration of 5 months. In both arms, a questionnaire and clinical assessment will take place at baseline and month 6.

During the baseline visit, the research optometrist takes note of the glaucoma medication dosing schedule (see Fig. 1) in the participant instruction booklet (see Additional file 1) to ensure a uniform presentation of adherence goals across participants. Medication adherence will be monitored during the whole 6-month period by means of electronic containers eCAPs™ (Information Mediary Corporation, Ottawa, ON, Canada). An eCAP™ is a medication event monitoring system with an inbuilt electronic tag which records the time whenever it is opened and closed. Each eye drop will be stored in separate vials with separate eCAPs™. At month 3, eCAPs™ are collected by a courier service, medication adherence is calculated for months 2 and 3 and the eCAPs™ are returned to the patients along with a short adherence report for that period (see Additional files 2 and 3). The next assessment period for medication adherence runs from months 4 to 6, and adherence calculation takes place after the patients returned their eCAPs™ at the month 6 study assessment. Patients also receive a call at the end of months 2 and 5 to verify that they understand their arm allocation and adherence goals, and that patients with multiple eye drops keep their medication in the assigned eCAP™.

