### Sample size

We chose to power the study to detect differences of ten percentage points in average monthly percentage of adherent days at 6 months between the two study arms. This effect size is sufficient to measure the effects reported by a majority of financial incentive studies [30] and is in line with a recent study that also used percentage adherence measured by electronic caps as primary end point [43]. In order to detect such effect size, a total of 100 participants is needed. This calculation assumes a two-sided statistical test of difference in means with a 5 % significance level and a power of 80 %. In addition, the standard deviation of the monthly percentage of adherent days is assumed to be no greater than 16.3 %, which is the maximum standard deviation in dose-rate adherence reported by Robin and colleagues [44]. Finally, attrition over the 6-month study is assumed to be no greater than 20 %.

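### The imputation model for missing month-6 adherence omits the adherence recorded in months 2–5, so it cannot correct the selective VP withdrawal that the protocol says might occur

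*Protocol article*

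**What the plan says.** Protocol article, Statistical methods, Primary analysis: change in percentage of adherent days at month 6 is regressed by OLS on arm, baseline percentage of adherent days, change in number of daily doses, and age, language, income, IOP, BIPQ and BMQ scores. On missing data it says: "Remaining missing adherence data will be imputed using Markov chain Monte Carlo multiple imputation including as predictors all factors mentioned above". A sensitivity analysis carries baseline adherence forward for patients who withdraw, because "those VP patients who do not achieve their goals might disproportionally withdraw from the study".

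Elsewhere the article shows that adherence between baseline and month 6 is available:
- Study arms: devices are collected at month 3 and "medication adherence is calculated for months 2 and 3"; patients then get a report. For VP patients the report shows the rebate earned (Arm 2).
- Secondary outcomes and Secondary analyses: monthly change is an outcome for months 2–5 and is modelled over months 2–6.
- Patient recruitment, retention, withdrawal, and discontinuation: a patient who withdraws is paid SGD15 for returning the device, so later months can sometimes be recovered.

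**The concern.** The feared reason for withdrawal, missing the adherence goal, is for many patients a recorded quantity. A VP patient who misses the first goal learns this from the month-3 report, and the trial team holds the same data. The listed predictors do not include it.

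Imputing the outcome from the same variables as the analysis model adds no information about who left. In expectation it gives the same estimate as a regression on completers. A VP patient who was failing at month 3 and then left is assigned the month-6 adherence of VP patients who stayed and had a similar baseline. Missing at random given the listed predictors is then false, and the primary estimate moves in favour of VP.

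**Working it through.** **1. The plan's own figure.** Inputs from Sample size: "differences of ten percentage points in average monthly percentage of adherent days at 6 months between the two study arms"; a "two-sided statistical test of difference in means with a 5 % significance level and a power of 80" %; "the standard deviation of the monthly percentage of adherent days is assumed to be no greater than 16.3" %; "attrition over the 6-month study is assumed to be no greater than 20" %; "a total of 100 participants is needed".

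n per arm = 2(1.960 + 0.842)² × 16.3² / 10² = 41.7, so 42 per arm and 84 evaluable. Allowing for attrition, 84 × 1.2 = 100.8 (101) or 84 / 0.8 = 105. With 40 completers per arm the standard error is 16.3 × √(2/40) = 3.64 points and power is 78.3%. The stated 100 is reproduced approximately, and this point does not affect it.

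**2. A hand formula for the bias.** Let d be the VP withdrawal fraction. Let G be the gap in mean month 2–3 adherence between VP completers and VP leavers at the same baseline. Let b be the slope of month 6 on month 2–3 adherence at the same baseline. The completers' mean exceeds the mean of all patients by d times the completer–leaver gap. So, with UC dropout unrelated to adherence,

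overstatement ≈ d × b × G.

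For equally correlated months with correlation ρ, b = (ρ − ρ²) / [(1 + ρ)/2 − ρ²]. At ρ = 0.5, b = 0.25/0.50 = 0.5. With simulated gaps G of 8.5, 8.3 and 13.2 points:
- d = 0.2: 0.2 × 0.5 × 8.5 = 0.85
- d = 0.3: 0.3 × 0.5 × 8.3 = 1.25
- d = 0.3, stronger selection: 0.3 × 0.5 × 13.2 = 1.98

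**3. Simulation.** 400,000 patients, SD 16.3, true effect 10. VP dropout is logistic in mean month 2–3 adherence; UC dropout is random unless stated. Assumed, not in the protocol: ρ from 0.3 to 0.7, selection slope 1 or 2 per SD, dropout 20/20 or 30/10 (VP/UC, %), and SD of individual response to the rebate 0 or 8. Results at ρ = 0.5:

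| Response SD | Slope | VP/UC dropout | Full data | Listed predictors | Plus months 2–3 | Baseline carried forward |
|---|---|---|---|---|---|---|
| 0 | 0 | 20/20 | 10.04 | 10.04 | 10.04 | 8.04 |
| 0 | 1 | 20/20 | 10.04 | 10.92 | 10.10 | 8.08 |
| 0 | 1 | 30/10 | 10.02 | 11.23 | 10.01 | 6.98 |
| 0 | 2 | 30/10 | 10.06 | 11.92 | 10.05 | 7.05 |
| 8 | 1 | 20/20 | 10.00 | 11.41 | 9.99 | 8.54 |
| 8 | 1 | 30/10 | 10.00 | 12.06 | 10.00 | 7.67 |
| 8 | 2 | 30/10 | 9.95 | 13.03 | 9.92 | 7.97 |
| 0 | 1, both arms | 20/20 | 10.07 | 10.09 | 10.10 | 8.09 |

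Rows 2–4 agree with the hand formula (0.88, 1.21 and 1.86 against 0.85, 1.25 and 1.98). Over all ρ with selective VP dropout, the listed predictors give 10.7–13.0, adding months 2–3 gives 9.9–10.1, and baseline carried forward gives 7.0–8.6. A milder pattern, in which VP patients below 75% leave at 30%, other VP patients at 5% and UC at 20%, gives 10.4–10.6 with the listed predictors.

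**4. Limit of the remedy.** If VP dropout depends directly on unobserved month-6 adherence, the listed predictors give 11.5–16.4 and adding months 2–3 gives 11.2–15.3.

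**5. Baseline carried forward.** With dropout unrelated to adherence and a common drift δ after baseline, its expected value is 10(1 − d_VP) + δ(d_UC − d_VP). At 30/10 this is 7.0 with δ = 0, and 7.0 + 2.0 = 9.0 with δ = −10. It depends on drift and the dropout split, not on how the leavers were doing.

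**The case against.** The best defence is that the text imputes adherence data generally, not only month 6, and that Secondary analyses applies the same approach to months 2–6. MCMC imputation is a multivariate method; if the monthly values are imputed together, months 2–5 inform month 6 automatically. That reading is possible, but the article does not state it. It names a predictor set for the primary analysis, and monthly adherence is not in it. One sentence would settle the matter.

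Four stronger readings are tempting, and the documents do not support them:
- *The primary result will be biased.* The protocol says only that selective withdrawal might occur. With dropout unrelated to adherence, or equally related in both arms, the bias is about zero.
- *The sensitivity analysis misses the problem.* Where dropout depends on month 2–3 adherence it moves the estimate down, to 7.0–8.6 without drift. In a run with downward drift and mainly VP withdrawals it gave 10.2, close to the true 10. The fair criticism is that its result depends on the scenario and that it also ignores months 2–5.
- *Month-3 data exist for everyone.* They exist for patients who reach the month-3 collection. A patient who leaves earlier without returning the device has no adherence data, not even baseline, so the remedy cannot help there.
- *Change in daily doses should leave the imputation because it is unknown for dropouts.* It is in the analysis model, so removing it from the imputation alone would make the two models inconsistent. It can be imputed jointly.

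Fully separate imputation by arm would also be fragile with about 40 completers per arm.

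**Conclusion.** The point holds as a conditional one. The stated predictor list omits the recorded data that best identify VP patients who miss their goals, and the protocol itself names their withdrawal as a risk. If it occurs, the primary analysis overstates the VP effect by roughly 0.5 to 3 points on a true 10. That compares with an unadjusted standard error of about 3.6 points at 40 completers per arm. The direction follows from the structure of the model. The size rests on assumed correlation, dropout split, selection strength and variation in response, none of which the protocol gives. Adding month 2–3 adherence removes the bias when dropout depends on those months, and only part of it when dropout depends on unobserved month-6 adherence.

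**What to change.** Amend the imputation sentence in Primary analysis to say that:
- all observed monthly adherence enters the imputation model: at minimum months 2–3 for patients who reach the month-3 collection, and later months where a withdrawing patient returns the device;
- the randomisation stratum (one versus multiple eye drops) enters it too;
- one way to do this is to impute months 1–6 jointly with arm included;
- change in daily doses stays in, imputed jointly where missing.

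Keep baseline carried forward as a sensitivity analysis, noting that its result depends on drift and the dropout split and that it does not use months 2–5. A delta-shift analysis is an optional addition, to cover dropout that depends on unobserved month-6 adherence.

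The cost is programming and a slightly larger imputation model for a trial of 100. No new data are needed.
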